### ***Etiological diagnostics***

Sputum can be cultivated to determine a specific bacterial infection. However, results are often first available after discharge of the patient or completion of treatment (9, 16). Therefore, better and faster methods are required. A so-called 'point-of-care' (POC) tool providing rapid microbiological results on e.g. sputum samples would be beneficial. Systems are available today based on PCR (polymerase chain reaction) methods with results available within one hour for a variety of viral and bacterial agents (34). The impact of such systems has not been investigated in an ED context.

The diagnosis of acute pyelonephritis is verified by significant bacteriuria (30), but up to half of the patients with clinical pyelonephritis fails to meet this diagnostic criterion. Unfortunately, the sample to result time for urine cultures are at last one day if negative – two to three days if positive. (29, 30, 35, 36) Urine test strips are unreliable with low specificity and low predictive values (37). Therefore, a POC tool is necessary, which can provide rapid results and quickly identify the many patients who do not have bacteria in the urine. One tool is urine flow cytometry, which has shown promising diagnostic value with a high negative predictive value for the exclusion of bacteriuria (38). However, better documentation for its use as an ED diagnostic screening method is vital.

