### ***Hypothesis, aim and objectives***

Our broad hypothesis is that by improving the knowledge of ED infected patients and by introducing new diagnostic tools, which contribute to the development of rapid and more accurate diagnosis of acute infections, a more appropriate antibiotic therapy can be administered.

The project aims to adapt and evaluate alternative diagnostic tools and working methods that support a prompt and accurate diagnosis of hospitalized patients suspected of an urgent infection – with special focus on pneumonia and acute pyelonephritis.

The research objectives are:

- 1) What is the patient characteristics and course of treatment of the different ED infections?
- 2) What is the diagnostic value of the infection markers PCT, suPAR, and CRP in patients with suspected pneumonia and pyelonephritis?
- 3) What is the diagnostic value of the lung injury markers SP-D, YKL-40, and KL-6 on diagnosing pneumonia
- 4) What is the impact of bedside-US and ULDCT on diagnosing pneumonia ?
- 5) What is the impact of advanced US on diagnosing pyelonephritis?
- 6) What is the impact of bedside-US on diagnosing hydronephrosis?
- 7) What is the impact of POC-PCR analysis of sputum on antibiotic prescriptions?
- 8) What is the impact of POC urinary flow cytometry on diagnosing and excluding bacteraemia?

The goal is to combine the results of all these eight objectives into one novel diagnostic model which the ED physician can apply when patients with suspicion of an infection is admitted.

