#### ***POC urine flow cytometry***

Within 4 hours from arrival, a urine sample will be collected according to routine procedure. The study assistant will be responsible for the collection to optimize compliance. Preferably a mid-ray urine or for catheter users (if possible) by introducing a clean catheter for optimal urine quality. The sample will be divided into two aliquots; one half for routine urine culturing in the Microbiological Department, and one half for POC urine flow cytometry analysis in the Biochemical Department.

The POC urine flow analysis is performed by the Sysmex UF -5000, a fully automated flow cytometry analyser for particle analysis in urine. It discriminates and counts 17 diagnostic parameters of cells and formed elements in urine. Particles are stained by specific flouorochromes for nucleic acids and for surface structures, and are exposed to a blue semi-conductor laser-light at 488 nm wavelength. Counting and classification is based on signals of forward scattered light (FSC), side scattered light (SSC), side fluorescent light (SFL), and depolarized side scattered light (DSS). The pattern of individual light signals is translated by algorithms allowing identification and classification into the particle categories, and results will be collected for bacteria, White Blood Cells (WBC), and Red Blood Cells (RBC). The light signals differ for Gram negatives and Gram positives, and this can be recognized by the analyser. For the above mentioned parameters, the analytical performance of the urine flow cytometer will be compared to the gold standard a urine culture on selective agar plates. A protocolled procedure for the collection and handling of samples will ensure consistent data quality.

The analysis will be carried out by laboratory assistants. The results of the POC urine flow cytometry analysis are not currently reckoned state-of-the-art and will be used for scientific purpose only. Results will be coded by the laboratory technician and not visible in the electronic laboratory system.

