### *Diagnostic value of POC urine flow cytometry*

Common urinary culture shows significant growth of uropathogenic bacterium in approximately 50% of people with suspected pyelonephritis (30). Asymptomatic bacteriuria accounts for about 20% in the elderly population, depending on gender and age (46), which among 1000 inpatients suspected of infection, of which 15% have pyelonephritis, gives a sensitivity of 50% (95% CI: 42-58 %) and a negative predictive value of 90% (95% CI: 77-83%). With the expectation of identifying at least 150 cases of pyelonephritis among 750 inpatients suspected of infection, an improvement in sensitivity to 70% (95% CI: 62-77%) and negative predictive value to 95% (95% CI: 93 -96%) could be found with 95% security.

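### Urine flow cytometry: the objective names bacteraemia, which no planned analysis uses, and urine culture is the gold standard in one section but the test to be beaten in another

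*Protocol*

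**What the plan says.** All four statements below are in the Protocol.

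- **Hypothesis, aim and objectives**, objective 8: "What is the impact of POC urinary flow cytometry on diagnosing and excluding bacteraemia". Bacteraemia is bacteria in the blood.
- **Etiological diagnostics** (background): the test is wanted because it has shown promise "with a high negative predictive value for the exclusion of bacteriuria". This concerns bacteria in the urine.
- **POC urine flow cytometry** (procedure): "the analytical performance of the urine flow cytometer will be compared to the gold standard a urine culture on selective agar plates". This is the only place that names a reference standard for flow cytometry.
- **Diagnostic value of POC urine flow cytometry** (outcomes): the baseline is culture, since "Common urinary culture shows significant growth of uropathogenic bacterium in approximately 50% of people with suspected pyelonephritis". The calculation continues "With the expectation of identifying at least 150 cases of pyelonephritis among 750 inpatients suspected of infection" and anticipates "an improvement in sensitivity to 70% (95% CI: 62-77%) and negative predictive value to 95" per cent. The condition being detected is pyelonephritis, culture is the test to improve on, and no reference standard is given.

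An expert-panel diagnosis of pyelonephritis is defined in the section on bedside and advanced ultrasound. It draws on all available relevant information and is not linked to flow cytometry.

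**The concern.** Target condition and reference standard define a diagnostic-accuracy question, and here neither is fixed.

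The stated objective points to blood culture as reference. Blood cultures are taken routinely, but neither flow cytometry section uses them. Once that word is set aside, a second problem remains: urine culture is the yardstick in the procedure section and the competitor in the outcome section.

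The practical risk is that a benchmark set for one condition is applied to another. An analyst who follows the procedure section computes sensitivity against culture and finds only the 50% and 70% figures to judge it by. A sensitivity of 70% against culture would then look like the planned success, although it means missing 30% of culture-positive patients, which is poor for a test meant to exclude bacteriuria. With the reference left open, it could also be chosen after the results are known. The result feeds the combined diagnostic model, where excluding bacteriuria, pyelonephritis or bacteraemia means different things to the physician.

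**Working it through.** **Inputs** (outcome section on flow cytometry): 1000 inpatients, 15% with pyelonephritis (150 cases, 850 non-cases); culture positive in about 50% of cases; "Asymptomatic bacteriuria accounts for about 20% in the elderly population", which the protocol in effect applies to all non-cases; target sensitivity 70% with 150 cases among 750.

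**1. Reproducing the plan's figures**
- Baseline sensitivity: 75/150 = 50% (Wald 95% CI 42.0 to 58.0%). Printed: 42-58%.
- Target sensitivity: 105/150 = 70% (Wilson 95% CI 62.2 to 76.8%). Printed: 62-77%.
- Baseline NPV: true negatives 0.80 × 850 = 680, false negatives 75, so 680/755 = 90.1%. Printed: 90%.

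The sensitivities and their intervals reproduce with the 150 pyelonephritis cases as denominator. The outcome section is therefore not a loosely worded comparison against culture.

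**2. Culture as reference**
- Culture-positives: 0.50 × 150 + 0.20 × 850 = 75 + 170 = 245. Culture-negatives: 1000 − 245 = 755. Only 75/245 = 31% of culture-positives have pyelonephritis.
- Culture against itself: sensitivity 245/245 = 100%, NPV 755/755 = 100%. Flow cytometry can tie but not improve.
- A sensitivity of 70% against culture would miss 0.30 × 245 = 73.5, about 74 culture-positive patients.

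**3. Pyelonephritis as reference**
- A cytometer identical to culture: 75/150 = 50%, no gain.
- Reaching 70% needs 105 detected cases, so at least 105 − 75 = 30 culture-negative cases must be flagged. Against culture each of these is a false positive.
- Power for 50% versus 70% in 150 cases, two-sided 5%: about 95% if treated as unpaired groups of 150. For the paired (McNemar) comparison, let c be the share positive on culture only (assumed, since the protocol gives no figure) and d = c + (c + 0.20) the discordant share. Power = Φ[(0.20√150 − 1.96√d)/√(d − 0.04)].

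| c | d | Power |
|---|---|---|
| 0 | 0.20 | >99% |
| 0.05 | 0.30 | >99% |
| 0.10 | 0.40 | 98% |
| 0.15 | 0.50 | 94% |

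The sensitivity gain is thus feasible against an independent pyelonephritis diagnosis.

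**4. Can one instrument do well on both?**
Suppose it flags all 245 culture-positives plus 30 culture-negative pyelonephritis cases.
- Against culture: sensitivity 245/245 = 100%, specificity (755 − 30)/755 = 725/755 = 96%, NPV 725/725 = 100%.
- Against pyelonephritis: sensitivity 105/150 = 70%.

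Yes, at a cost of 4 points of specificity against culture.

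**Side note on the same sentences.** The printed CI of 77-83% for the 90% NPV excludes its own estimate and matches the CI of the 80% specificity (680/850). An NPV of 95% with 150 × 0.30 = 45 false negatives needs 0.95 × 45/0.05 = 855 true negatives, but 750 patients include only 600 non-cases, so the ceiling is 600/645 = 93.0%. These figures need correcting in their own right; the present point does not depend on them.

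**The case against.** The best defence is that these are two different questions. The procedure section speaks of analytical performance, the outcome section of diagnostic value, and validating a counter against culture while judging its clinical accuracy against disease is legitimate. The outcome section does not import culture as its reference, and its denominator is clearly pyelonephritis. Flow cytometry also reports white and red cells, so it need not merely reproduce growth. Bacteraemia is most plausibly a slip for bacteriuria, since no flow cytometry calculation or procedure uses it.

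Much of this stands. A reader might infer that the targets are incompatible, that a cytometer good enough to exclude bacteriuria must fail the 70% target, or that no analysis could answer the objective. The documents do not support that. Step 4 shows one instrument satisfying both references, and the failure applies only to an exact copy of culture. The improvement is impossible only if the procedure section's reference is carried into the outcome section.

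What does not stand is the suggestion that nothing needs changing. The protocol never says there are two analyses, the outcome section names no reference standard, and the panel diagnosis is not tied to this test. An analysis plan could rank two stated analyses, but to use the objective as worded it would have to overrule the protocol.

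**Conclusion.** The point holds as an error of specification. Objective 8 names a condition that no planned flow cytometry analysis uses, and urine culture is reference standard in one section and comparator in another. With culture as reference, the rise from 50% to 70% cannot be shown, because culture's own sensitivity is 100% by construction. It can be shown only against a pyelonephritis diagnosis that does not rest on culture, where 150 cases give ample power (about 94% or more over the assumed discordance range).

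The size of the mismatch is 100% versus 50% for a cytometer identical to culture. This rests on two of the protocol's own simplifications: that the 50% positivity among suspected cases is culture's sensitivity in true cases, and that the 20% bacteriuria rate for the elderly applies to all non-cases. The impossibility against culture depends on neither.

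**What to change.** 1. In objective 8, change bacteraemia to bacteriuria, in line with the background section, once the sponsor confirms that this was meant.
2. In the outcome section, state two analyses:
   - (a) Flow cytometry against significant growth on urine culture: sensitivity, specificity and NPV. Drop the 50%/70% benchmark here.
   - (b) Flow cytometry versus culture as a paired comparison, with the expert-panel pyelonephritis diagnosis as reference for both. The 50% to 70% figure applies here only.
3. State which is primary. Either choice is defensible; leaving it open is not.
4. Acknowledge that a panel that sees the culture result favours culture in (b).
5. Give (a) its own precision statement. With 245 culture-positives per 1000, the 95% half-width is 1.96√(p(1 − p)/245): 2.7 points at an assumed sensitivity of 95% and 3.8 points at 90%. With 750 patients of whom 150 are cases, culture-positives are 75 + 0.20 × 600 = 195, and the half-widths are 3.1 and 4.2 points.

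**Cost.** Wording and a short precision calculation; no new samples or tests. A gain over culture can no longer be claimed from the culture-referenced analysis. If specificity or NPV is wanted in (b), the panel diagnosis must also cover patients without pyelonephritis, and the protocol does not say whether it does.

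### The planned gain of urine flow cytometry over culture is stated as sensitivity and NPV with no specificity or cut-off, and the two target values cannot occur together at 150 cases in 750

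*Protocol*

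**What the plan says.** The only analysis text for this test is the section Diagnostic value of POC urine flow cytometry. It first describes culture. It notes that "Asymptomatic bacteriuria accounts for about 20% in the elderly population", and it takes a cohort of 1000, "of which 15% have pyelonephritis, gives a sensitivity of 50% (95% CI: 42-58 %) and a negative predictive value of 90" per cent. It then changes the denominator: "With the expectation of identifying at least 150 cases of pyelonephritis among 750 inpatients suspected of infection". For those numbers the target set for flow cytometry is "an improvement in sensitivity to 70% (95% CI: 62-77%) and negative predictive value to 95" per cent, the NPV with an interval of 93 to 96%. No specificity, likelihood ratio, AUC or cut-off is named for flow cytometry.

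The procedure section POC urine flow cytometry describes an analyser that counts particles: "results will be collected for bacteria, White Blood Cells (WBC), and Red Blood Cells (RBC". Both tests use the same urine: "The sample will be divided into two aliquots; one half for routine urine culturing in the Microbiological Department", the other half for flow cytometry. The same section says that "the analytical performance of the urine flow cytometer will be compared to the gold standard a urine culture on selective agar plates".

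The protocol treats its other index tests differently. The imaging sections list specificity, likelihood ratios and AUC, and the infection-marker section plans ROC curves and a search for a cut-off.

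**The concern.** A count has no sensitivity until a cut-off is chosen. Culture is entered at one operating point, with a specificity behind it; flow cytometry is entered by two measures that both improve when the cut-off is lowered. Nothing in that pair limits the loss of specificity, so the two tests may end up compared at very different specificities.

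The stake is the purpose of the test. The Background (Etiological diagnostics) wants a rapid tool that recognises the large group without bacteriuria, and objective 8 covers diagnosing as well as excluding. How many patients are cleared depends mainly on specificity. A cut-off that clears few patients could still show higher sensitivity and higher NPV than culture.

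**Working it through.** **Inputs.** From the protocol: culture sensitivity 50%; 20% asymptomatic bacteriuria, read as 80% specificity; 150 cases in 1000 (15%) and then 150 in 750 (20%); targets of 70% sensitivity and 95% NPV. Assumed for illustration only: equal-variance binormal counts and an AUC of 0.70.

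NPV = Sp(1−p) / [Sp(1−p) + (1−Se)p], where p is prevalence.

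**1. Culture baseline (150 in 1000).**
- Sensitivity 75/150 = 50%, interval 42–58%: reproduces.
- True negatives 0.80 × 850 = 680, false negatives 75. NPV = 680/755 = 90.1%: reproduces, so 80% specificity is what was used.
- The interval for 680/755 is 88–92%. The printed 77–83% is the interval for 680/850 = 80%, the specificity. It is attached to the wrong measure and excludes its own 90%.

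**2. Flow cytometry target.**
- Sensitivity 105/150 = 70%, interval 62–77%: reproduces.
- NPV at 150 in 750: 45 false negatives and at most 600 true negatives, so at most 600/645 = 93.0%. At 80% specificity it is 480/525 = 91.4%. The printed 95% does not reproduce.
- NPV at 150 in 1000: at most 850/895 = 94.97%, interval 93–96%. The printed figures match this denominator with near-perfect specificity. Rounding to 95% needs Sp ≥ 0.945 × 0.15 × 0.30 / (0.055 × 0.85) = 91%.

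**3. Lowering the cut-off.** For AUC 0.70, d = √2 × z(0.70) = 0.742. At culture's 80% specificity, sensitivity is Φ(0.742 − 0.842) = 46%, below culture's 50%. On the same model culture's point (50%, 80%) corresponds to AUC 0.724. With Sp = Φ(d − z(Se)):

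| Sensitivity | Specificity | NPV at 15% | NPV at 20% |
|---|---|---|---|
| 70% | 58.6% | 91.7% | 88.7% |
| 80% | 46.0% | 92.9% | 90.2% |
| 95% | 18.3% | 95.4% | 93.6% |
| 98% | 9.5% | 96.4% | 94.99% |
| 99% | 5.7% | 97.0% | 95.8% |

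Both targets are met at 95% sensitivity (15% prevalence) or just above 98% (20%). At 95% sensitivity and 15% prevalence the share ruled out is 0.85 × 0.183 + 0.15 × 0.05 = 16.3%, against 755/1000 = 75.5% for culture.

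**4. Check without the binormal model.** At 15% prevalence and 95% sensitivity, NPV is 95.0% when Sp = 0.95 × 0.15 × 0.05 / (0.05 × 0.85) = 16.8%. The Youden index is 0.95 + 0.168 − 1 = 0.12, against 0.50 + 0.80 − 1 = 0.30 for culture. A test with culture's Youden index or lower can reach 95% NPV once sensitivity is at least about 87% (15% prevalence) or 92% (20%).

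**5. Pairing.** With 150 cases, 80% power and two-sided 5%, the McNemar normal approximation detects a gain in sensitivity of about 10 points (20% discordant, assumed) to 14 points (40% discordant). An unpaired comparison from 50% detects about 16.

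**The case against.** The section is written as a precision statement: it says what could be found with the planned numbers. It declares no primary outcome, test or rule for claiming superiority. A reader might infer that flow cytometry will be judged on sensitivity and NPV alone and that a worse test would then pass. The document does not support that. Sensitivity and NPV are proper measures for a rule-out test, and an analysis plan that is not shown may fix a cut-off and add specificity.

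The printed pair itself does not describe a worse test. At 70% sensitivity and 15% prevalence, an NPV that rounds to 95% implies specificity of about 91% or more, which is better than culture on both axes. The weak-test scenario needs the targets read as floors and a cut-off well beyond the printed 62–77% interval. A pure chance test could not pass, because its NPV stays at 85% or 80%.

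A reader might also infer an unpaired test from the separate intervals. None is prescribed, and planning without pairing is conservative.

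These objections stand and limit the point. They do not remove two things that the protocol itself prints: a comparison in which specificity lies behind culture's figures but is left open for flow cytometry, and a target pair that cannot occur at the stated 150 in 750.

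**Conclusion.** The point holds at moderate severity. The comparison with culture is framed by two measures that both favour a low cut-off, with nothing that bounds specificity. The targets also disagree with their own denominator: NPV is at most 93.0% at 70% sensitivity in 150 of 750. That second part is arithmetic and needs no assumption.

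The first part rests on reading the targets as minimum values and on a proper ROC curve; an irregular curve could break the rise in NPV locally. The figures of 95% sensitivity, 95.4% NPV and 18% specificity illustrate the mechanism for an assumed binormal AUC of 0.70 and do not predict this analyser's performance. The gain from pairing is a secondary matter of precision.

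**What to change.** In Diagnostic value of POC urine flow cytometry:

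- Make the comparison the paired difference in sensitivity between flow cytometry and culture, both against the pyelonephritis reference diagnosis in the same patients. Take it either at culture's observed specificity, with a bootstrap interval that repeats the matching in each resample, or at a cut-off fixed before analysis, with McNemar's test.
- Report specificity and the share of patients ruled out next to NPV.
- Restate the target sensitivity, specificity and NPV so that they agree at one prevalence, and correct the interval printed for culture's NPV.
- Reconcile this with the procedure section, which makes culture the gold standard. Where culture is the reference it has no sensitivity of its own, so there report flow cytometry's sensitivity, specificity and NPV at the pre-fixed cut-off and make no claim of improvement over culture.

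The cost is wording and a little more analysis; no new data are needed. The downside is that flow cytometry's reported sensitivity will be lower than at a freely chosen low cut-off.

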## **Ethical considerations and risks**

The study is reported to the Scientific Ethics Committee and verbal and written consent for participation from patients is collected. The study are also reported to the Data Inspectorate and registered in ClinicalTrial.com. The study is part of Patient Data Explorative Networking (OPEN). Approval from The Danish Data protection agency for the research biobank has been applied for. Personal information will not be sent abroad.

The collection of blood will be done in relation to planned blood sampling in clinical routine. Blood sampling may cause slight bruising. The collection of urine may be unpleasant. The collection of clinical information may cause nervousness. We will try to minimize these discomforts by engaging with participants about the procedures by the study staff members.

Participation in track A and B will contain additional imaging. Patients under the age of 40 are excluded from the track A due to the extra risk of developing a deadly cancer due to radiation from HRCT. A typical HRCT gives a radiation dose of approximately 2.2 mSv which corresponds to a cancer risk of 1:9100. An X-ray gives a radiation dose of approximately 0.06 mSv which corresponds to a cancer risk of 1:333330. An ULDCT gives a radiation dose of approximately 0.1 mSv which corresponds to a cancer risk of 1:200000. Participation in track A give each participant approximately 2.26 mSv (ULDCT and HRCT) which corresponds to a cancer risk of 1:8850. The examination time of ULDCT and HRCT is approximately 10 minutes.

Patients included in the track B will undergo CEUS and an MRI. The US contrast agent consists of multiple microscopic gas bubbles in a stabilizing shell. These gas bubbles are eliminated with respiration through the lungs. Thus, in contrast to other contrasts used for MRI or CT, it is a non-nephrotoxic substance. Use of US contrast in rare cases cause allergic reactions; less than 1/10.000 exponents require medical treatment due to allergic reaction (47). The examination time of advanced US is approximately 20 minutes. MRI does not provide any radiation dose to the patients. Usual contraindications for MRI also apply in this study, thus we will exclude patients with i.e. claustrophobia or contraindicating metal implanted in the body. The examination time of the MRI is approximately 45 minutes, which the participants are made aware of.

The consent gives the researcher responsible for the study, the sponsor, sponsor's representatives, and control authority direct access to obtain information in the patient medical record. This in order to find data about the patient's health status, which is necessary for the implementation of the study as well as for control purposes, including self-monitoring, quality control, and quality monitoring which is obliged to perform.

The risks and benefits taken into consideration, the overall risk for the participants is minimal, and furthermore, chances are that e.g. the additional diagnostic imaging may inform the clinician in a favorable way before the onset of patient treatment.

